## Abstract

**Introduction:**

High-risk non-muscle invasive bladder cancer (HRNMIBC) is a heterogeneous disease that can be difficult to predict. While around 25% of cancers progress to invasion and metastases, the remaining majority of tumours remain within the bladder. It is uncertain whether patients with HRNMIBC are better treated with intravesical maintenance BCG (mBCG) immunotherapy or primary radical cystectomy (RC). A definitive randomised controlled trial (RCT) is needed to compare these two different treatments but may be difficult to recruit to and has not been attempted to date. Before undertaking such an RCT, it is important to understand whether such a comparison is possible and how best to achieve it.

**Methods and analysis:**

BRAVO is a multi-centre, parallel-group, mixed-methods, individually randomised, controlled, feasibility study for patients with HRNMIBC. Participants will be randomised to receive either mBCG immunotherapy or RC. The primary objective is to assess the feasibility and acceptability of performing the definitive phase III trial via estimation of eligibility and recruitment rates, assessing uptake of allocated treatment and compliance with mBCG, determining quality-of-life questionnaire completion rates and exploring reasons expressed by patients for declining recruitment into the study. We aim to recruit 60 participants from six centres in the UK. Surgical trials with disparate treatment options find recruitment challenging from both the patient and clinician perspective. By building on the experiences of other similar trials through implementing a comprehensive training package aimed at clinicians to address these challenges (qualitative substudy), we hope that we can demonstrate that a phase III trial is feasible.

**Ethics and dissemination:**

The study has ethical approval (16/YH/0268). Findings will be made available to patients, clinicians, the funders and the National Health Service through traditional publishing and social media.

**Trial registration number:**

ISRCTN12509361; Pre results.

Strengths and limitations of this studyThis is an important comparison that has not been attempted before.This study will not determine which intervention is the superior treatment; a definitive phase III trial will still be needed.Recruitment may be challenging and may not be possible through traditional care pathways.

## Introduction

### Context

Bladder cancer (BC) is a common disease that is one of the most expensive malignancies to manage.^1^ Around 25% of patients present with poorly differentiated, low-stage tumours, termed ‘high-risk non-muscle invasive bladder cancer’ (HRNMIBC; including tumours with carcinoma in situ, invasion into the lamina propria and intraepithelial spread into the prostatic urethra). The two main treatment options for HRNMIBC are intravesical immunotherapy (using a maintenance regime of intravesical maintenance BCG (mBCG)) and radical cystectomy (RC). The former aims to induce an immune response against the tumour and may reduce the risk of progression to muscle invasion.^2^ While mBCG avoids bladder removal, it leaves patients at risk of local progression and may impact on quality of life (QoL) through local symptoms and anxiety. RC removes the risk of local disease progression and may have the best oncological outcomes but could be overtreatment for non-progressing tumours. Many patients develop short-term postoperative complications after RC, and others have a reduction in QoL following surgery. To date, RC and mBCG have not been directly compared. Their comparative risks and benefits are unknown, hampering decision making, clinical care and exposing patients to both overtreatment and undertreatment.

### Current knowledge

The natural history of HRNMIBC is unpredictable. Rates of progression to muscle invasion and metastases vary between 25% and 75%,^3^ and long-term outcomes suggest around 20%–25% of patients with HRNMIBC may die from BC.^4 5^ mBCG avoids bladder removal, and meta-analyses report potential reductions in progression by 5% at 2.5 years^6^. However, mBCG can be poorly tolerated, its impact on progression is debated^2^ and there are manufacturing problems.^7^ mBCG involves 27 intravesical instillations and 10 cystoscopies over 3 years. Many (74%) patients report local and systemic toxicity,^8 9^ so only 30% of patients complete mBCG.^9 10^ Furthermore, there are few data to support that mBCG with bladder preservation preserves a good QoL. With regards to oncological outcomes, reports of BCs failing mBCG find upstaging to invasion in 27%–63% of tumours and the cancer-specific survival is worse than for BC with de novo muscle invasion (eg, 37% vs 67%/3 years).^11–15^ RC includes removal of the bladder and adjacent organs and reconstruction of urinary drainage. Many patients develop short-term bowel, respiratory or cardiovascular problems, including up to 20% require intervention.^16^ Prospective studies report that recovery of QoL following RC takes 6 months or longer to recover to preoperative levels.^17^ Recurrence-free survival rates following primary RC for HRNMIBC cancers appear superior to those from mBCG (eg, 79%/10 years).^18^

### Surgical RCTs

As contemporary data challenge the role of mBCG^2^ and lessons have been learnt from large surgical randomised controlled trials (RCTs),^19^ we believe it is time to compare mBCG with RC. This is an important comparison, and this opportunity may be lost as RC for HRNMIBC becomes more popular.^20^ Importantly, the 2015 NICE BC guidelines selected this comparison as one of the highest-ranked research priorities in the disease.^21^ The BRAVO study aims to compare surgical and non-surgical treatments. Trials of similarly disparate treatments in BC have previously failed to recruit (eg, CRUK-SPARE trial).^22 23^ Here we propose the preliminary work necessary to understand if we can undertake a large RCT of mBCG versus RC. Anticipated barriers to recruitment include patient and clinician preferences, BC treatment pathways, a lack of high-quality information^24 25^ and the need for staff training in equipoise and communicating RCT methods.^26^ To address these issues, we will develop a tailored staff training package to facilitate informed decision making about participation and to better understand RCT methodology. The development work will be informed by existing knowledge^24 27 28^ and context-specific evidence derived from interviews with patients and healthcare staff exploring: (a) treatment perceptions, (b) patient pathways to treatment, (c) barriers to participation and (d) training needs of site staff. This qualitative work to develop and deliver the training package is described in a separate protocol (see online supplementary file 1). We will then undertake a feasibility study to assess whether recruitment could be achieved in a definitive trial, embedding a qualitative component to establish patient experience.

10.1136/bmjopen-2017-017913.supp1Supplementary file 1

### Study aims

Our aims are to assess whether a larger phase III RCT is possible and to acquire sufficient 129 data to aid planning such a trial. Primary outcomes are: To assess the number of patients screened and identified as eligible within these six centres.To assess recruitment rates (number of patients randomised per month).

Secondary outcomes are:To assess acceptance of allocated treatment.To assess the rate of compliance with mBCG at 12 months after randomisation and collect reasons for non-compliance.To assess the feasibility and optimal frequency of collecting QoL data in patients treated for HRNMIBC.To obtain preliminary data on the QoL data of patients treated for HRNMIBC.To explore the reasons expressed by patients for declining recruitment into the study.

## Methods and design

### Trial design

BRAVO is a multi-centre, parallel-group, mixed-methods, individually randomised, controlled feasibility study in patients with HRNMIBC suitable for treatment by either mBCG or RC. Eligible, consenting patients will be randomised (1:1) to receive either mBCG or RC (figure 1). Due to the different treatment modalities in the two arms, it is not feasible to blind patients or clinicians to treatment allocation. Patient reported outcome data will be collected at 3, 6 and 12 months postrandomisation in clinic or by postal questionnaire if the patient is not due to attend a clinic visit.

**Figure 1 F1:**
[figure not shown]
Study flow diagram. HRNMIBC, high-risk non-muscle invasive bladder cancer; IVU, intravenous urogram; MDT, multidisciplinary team; QoL, quality of life; TURBT, transurethral resection of bladder tumour.

### Trial population

We aim to recruit 60 patients from six UK cancer centres and their associated district general hospitals. The inclusion criteria are:Male or female aged ≥18 years old.Patients with a new diagnosis of high-risk (high-grade^29^ or grade 3^30^ non-muscle invasive urothelial carcinoma (staged as pTa, pTis or pT1). Patients with previous low-grade non-muscle invasive bladder cancer (NMIBC) are eligible.The tumour is either solely urothelial cell carcinoma (UCC) or has UCC as the majority histological component.In addition to the HRNMIBC bladder tumour, there needs to be one or more risk factor from:presence of pTis in the bladderpresence of pTis in the prostatic urethralymphovascular invasionvascular invasionresidual grade 3/high-grade UCC on re-resection (or initial transurethral resection of bladder tumour (TURBT) if no re-resection)multifocal disease (>3 tumours at initial resection)young age (<65 years old)initial tumour size >3 cm (or >5 g in histology specimen)pT1 stage.Either re-resection of the bladder (following the initial diagnostic TURBT) within the 3 months prior to randomisation confirming the absence of muscle invasionORthe initial diagnostic TURBT biopsy contains muscle, ANDthe radiological and pathological stage assessment are in agreement regarding stage and absence of muscle invasion, ANDa re-resection is not appropriate in the opinion of the treating clinician ANDthe initial TURBT is within 3 months prior to randomisation.CT or cross-sectional imaging of the abdomen and pelvis within the year prior to starting treatment.Imaging of the lungs and thorax within 3 months prior to randomisation.Suitable and fit for both mBCG and RC as determined by the treating clinician.Central multidisciplinary team (MDT) pathological review agrees with diagnosis.If female, must be (as documented in patient notes):postmenopausal (no menses for 12 months without an alternative medical cause) orsurgically sterile (hysterectomy, bilateral salpingectomy or bilateral oophorectomy) orusing acceptable contraception (which must be continued for 7 days after the last dose of BCG or until RC is carried out). Women of childbearing potential must undergo a pregnancy test before randomisation.not breast feeding.

The exclusion criteria are:solely non-urothelial or any variant urothelial pathologyunable or not willing to give informed consentprevious high-risk (high grade or grade 3) non muscle invasive (NMI) or invasive BCany previous treatment with intravesical BCGany previous treatment with pelvic radiotherapyany other malignancy (excluding non-melanomatous skin cancer, low-risk prostate cancer and prior low-risk BC).

Eligibility waivers are not permitted.

Prior to entry, patients must be accurately staged (eg, cross-sectional imaging (eg, CT) of the abdomen, pelvis and thorax, or bone scan if indicated, within 3 months prior to randomisation) and judged to be eligible for both treatments (anaesthetic evaluation in those with borderline fitness for RC). After trial entry, women of childbearing age must be proven to be not pregnant (pregnancy test).

### Sample size

The sample size for this feasibility study has been set to give confidence that the recruitment target for the main trial can be met. A formal power calculation is not appropriate as effectiveness is not being evaluated. It is estimated that, per year, over the six centres, there will be approximately 1000 new diagnoses of NMIBC, where 20% are likely to be eligible (200 patients).^31^ We would need to show that we are able to randomise approximately 25% of all eligible patients to be confident that the recruitment target for the main trial would be met within 3 years, with an additional nine centres. We therefore plan to recruit 60 patients over an 18-month period in the feasibility study. For the phase III trial, we anticipate either a single primary endpoint (cancer-specific survival) or coprimary endpoints (cancer-specific survival and averaged quality-adjusted life years (QALYs)). We estimate that 506 participants are required to have 80% power to show a superiority HR of 0.626 (based on an improvement in 5-year cancer-specific survival from 70% in the BCG arm to 80% in the RC arm), assuming a 3-year accrual period, 5 years of follow-up and accounting for 5% loss-to-follow-up.

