### Criteria for progression to the definitive phase III trial

The following guidelines for progression to a definitive phase III trial have been defined:The recruitment and follow-up rates must demonstrate that a definitive trial using similar procedures will achieve sufficient power to test the hypothesised difference between treatment arms.The sample size calculation for the feasibility study and proposed phase III trial are provided earlier. This assumes that 20% of all new diagnoses of NMIBC would be eligible and approximately 25% of those would be randomised. To proceed to a definitive trial, we need to show that at least 20% of eligible patients can be randomised.

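### The main-trial recruitment projection falls short of 506 unless the nine added centres are much larger than the first six, and the 20% progression floor widens the gap

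*Protocol article*

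**What the plan says.** The Sample size section of the protocol article estimates that "per year, over the six centres, there will be approximately 1000 new diagnoses of NMIBC", of which 20%, or 200 patients, would be eligible. It continues: "We would need to show that we are able to randomise approximately 25% of all eligible patients" in order to be confident that "the recruitment target for the main trial would be met within 3 years, with an additional nine centres". It then draws the feasibility target from this: "We therefore plan to recruit 60 patients over an 18-month period in the feasibility study".

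The main-trial target follows in the same section: "We estimate that 506 participants are required to have 80% power to show a superiority HR of 0.626". The hazard ratio corresponds to cancer-specific survival at 5 years of 70% with BCG against 80% with RC, and the calculation takes 3 years of accrual, 5 years of follow-up and 5% loss.

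The section on criteria for progression gives two guidelines. The first is qualitative: recruitment and follow-up must show that a definitive trial run in a similar way would be adequately powered. The second repeats the 20% eligible and 25% randomised assumptions, then sets a lower floor: "we need to show that at least 20% of eligible patients can be randomised".

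**The concern.** The article gives every input to the recruitment projection except the volume of the nine added centres. Using the only volume it does give, neither the 25% planning rate nor the 20% floor reaches 506 in 3 years at 15 centres.

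Judging whether the main trial can recruit is the purpose of this study. If the planning rate and the numeric floor do not correspond to the design they are meant to support, an observed rate cannot be read as evidence for that design. A result in the expected region of 20% to 25% would satisfy the numeric floor while leaving the 15-centre, 3-year plan well short.

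**Working it through.** **Step 1. Reproduce the target of 506.** Inputs are from the Sample size section. Alpha is not stated, so two-sided 0.05 is an assumption, as is 1:1 allocation in phase III.

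- Hazard ratio: ln(0.80)/ln(0.70) = 0.6256, which rounds to 0.626.
- Events (Freedman): (1.96 + 0.8416)² × [(1 + 0.626)/(1 − 0.626)]² = 7.849 × 18.90 = 148.4, so 149.
- Event probability under exponential survival, 3 years of uniform accrual and 5 further years of follow-up: 1 − (e^(−5λ) − e^(−8λ))/(3λ). With λ = −ln(0.70)/5 = 0.0713 this is 0.370; with λ = −ln(0.80)/5 = 0.0446 it is 0.251. The mean is 0.3105.
- N = 149/0.3105 = 480, and 480/0.95 = 506 after rounding up.

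The stated figure is reproduced exactly. (Schoenfeld's formula gives 144 events and 489 patients.) The target is therefore not the problem.

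**Step 2. Project recruitment.** Eligible per centre-year: 1000 × 0.20/6 = 33.3. Centres: 6 + 9 = 15. Over 3 years that is 45 centre-years and 33.3 × 45 = 1500 eligible patients, *if the added centres match the average of the first six*.

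| Rate | Randomised in 3 years | Shortfall from 506 | Years needed at 15 centres | Centres needed for 3 years |
|---|---|---|---|---|
| 25% | 0.25 × 1500 = 375 | 131 (26%) | 506/125 = 4.0 | 506/25 = 20.2, so 21 |
| 20% | 0.20 × 1500 = 300 | 206 (41%) | 506/100 = 5.1 | 506/20 = 25.3, so 26 |

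The rate needed for the stated plan is 506/1500 = 33.7%. All of this takes the 15 centres as open from the first day, which favours the plan.

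**Step 3. Vary the unstated volume.** Let k be the average volume of an added centre relative to the first six. Recruitment is 150 + 225k at 25% and 120 + 180k at 20%.

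| k | 25% | 20% |
|---|---|---|
| 0.75 | 319 | 255 |
| 1.0 | 375 | 300 |
| 1.5 | 488 | 390 |
| 2.0 | 600 | 480 |

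The target is met at k = (506 − 150)/225 = 1.58 for 25%, and k = (506 − 120)/180 = 2.14 for 20%.

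**Step 4. Count the feasibility patients.** The article does not say that they count towards 506. Adding 60 gives 435 (25%) or 360 (20%). Adding the 75 that a true 25% rate would produce in 18 months gives 375 + 75 = 450. None reaches 506.

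**Step 5. Check the feasibility target.** Six centres over 18 months see 200 × 1.5 = 300 eligible patients. 25% of these is 75; the planned 60 is 60/300 = 20%. Scaled up, 60/(6 × 18) = 0.56 per centre-month, and 0.56 × 15 × 36 = 300 (using the unrounded rate).

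**Step 6. Power if accrual stopped at 3 years.** With events in proportion to N, 149 × 375/506 = 110 and 149 × 300/506 = 88. Power is Φ(√events × 0.374/1.626 − 1.96). This gives Φ(0.46), about 68%, at 375 and Φ(0.20), about 58%, at 300.

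**The case against.** The strongest reply is that equal volume at the added centres is the reader's assumption. The article is silent on it, and larger centres could close the gap. This stands as a limit on the claim: 375 and 300 are conditional figures. It does not remove the point. The centres would have to be about 1.6 or 2.1 times as large, nothing in the article says so, and the Setting section describes the present region as one of high bladder cancer incidence.

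A reader might go further and infer that a 20% result would make the sponsor launch a trial that its own figures show cannot recruit. The article does not support that. The 20% figure is a minimum among guidelines, and the first guideline separately asks whether recruitment supports a powered trial; a 20% rate that could not deliver the required number would fail it. The phase III figures are also provisional: the Statistical analyses and Discussion sections say that survival, eligibility and acceptance data from this study will feed the main-trial sample size. No passage commits anyone to 15 centres and a hard stop at 3 years, so the power figures in step 6 illustrate the size of the gap and are not a forecast.

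The 25% is given as approximate, but rounding does not stretch to 33.7%. Nor does the provisional status of phase III excuse a floor that disagrees with the design it is set beside.

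**Conclusion.** The point holds in conditional form. With added centres like the first six, the stated plan delivers 74% of its target at the planning rate (375/506) and 59% at the floor (300/506). The shortfall in patients does not depend on alpha or on the survival assumptions; only the power figures do.

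Two inconsistencies sit alongside it. The inference from 25% to 60 patients does not follow, because 60 corresponds to 20%. And for the stated 15-centre, 3-year design, the numeric floor is looser than the article's own guideline on adequate power: on the equal-volume assumption, any rate from 20% up to about 34% satisfies the floor without supporting that design. No estimate or analysis in the feasibility study itself is affected.

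**What to change.** - **Sample size section.** Keep the feasibility target of 60. Restate the main-trial plan that each rate supports: about 21 centres or 4.0 years at 25%, and about 26 centres or 5.1 years at 20%. Alternatively, state and justify the larger eligible volume assumed for the nine added centres.
- **Same section.** Correct the link between 25% and 60 patients: 60 in 18 months corresponds to 20% of about 300 eligible, and 25% would be 75.
- **Criteria for progression.** State that a rate between 20% and about 34% supports progression only with the larger number of centres or the longer accrual, so that the numeric floor agrees with the guideline on power. If larger added centres are justified instead, recompute the upper figure from their volume.

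Simply raising the floor to 34% is not a good alternative. It would need about 0.337 × 300 = 101 patients randomised in 18 months, so a study that met its own target of 60 would fail automatically.

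The cost is a change of wording in two sections, with no additional feasibility patients. The downside is that the main-trial plan looks less favourable, with more centres or longer accrual than now stated.

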### Trial status

The trial opened to recruitment in October 2016 using protocol version 2.0 (8 October 2016) and is due to close in March 2018.

The protocol was amended to version 3 in October 2016 to account for additional inclusion and exclusion criteria and updated surgeon accreditation criteria. The protocol was amended to version 4 in November 2016 to further update the inclusion criteria and surgeon accreditation criteria. Both amendments were reviewed and approved by the sponsor and the National Research Ethics Service Committee Yorkshire & Humber–South Yorkshire (reference no. 16/YH/0268). Protocol amendments are disseminated to relevant parties by CTRU.

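### Sixty patients in 18 months is 20% of the expected eligible pool, not the 25% it is said to follow from, and the 20% progression minimum is not reconciled with that 25%

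*Protocol article*

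**What the plan says.** The Sample size section of the protocol article builds the target in three steps. It first gives the yearly pool over the six centres: "there will be approximately 1000 new diagnoses of NMIBC, where 20% are likely to be eligible (200 patients"). It then states the requirement for the main trial to recruit within 3 years with nine further centres: "We would need to show that we are able to randomise approximately 25% of all eligible patients to be confident". Finally it draws the conclusion: "We therefore plan to recruit 60 patients over an 18-month period in the feasibility study". The same section puts the definitive trial at 506 participants.

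The Trial status section agrees with the 18-month period: "The trial opened to recruitment in October 2016 using protocol version 2.0 (8 October 2016) and is due to close in March 2018".

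The section on criteria for progression lists guidelines. One is that recruitment and follow-up must be shown to be good enough for the definitive trial to have sufficient power. It also restates the planning assumption, "This assumes that 20% of all new diagnoses of NMIBC would be eligible and approximately 25% of those would be randomised", and follows it directly with the minimum: "To proceed to a definitive trial, we need to show that at least 20% of eligible patients can be randomised".

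**The concern.** The target of 60 is presented as a consequence of the 25% requirement, but the stated pool and period give a different number. The two sections also name different proportions that the study needs to show, 25% in one and 20% in the other, with nothing to connect them.

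Recruitment is a primary outcome, and the feasibility sample size is justified by the confidence it gives in recruiting to the main trial. If the target, the requirement and the minimum do not agree, a result between the two proportions has no agreed reading. The choice between them could then be made after the result is known.

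**Working it through.** **Inputs.** About 1000 new diagnoses a year, 20% eligible, about 25% of eligible patients randomised, 60 patients, 18 months, and 506 participants in 3 years with nine added centres (all Sample size). The 20% minimum comes from the criteria for progression.

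**Step 1: the yearly pool.** 1000 × 0.20 = 200 eligible a year. This reproduces the article's figure.

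**Step 2: the pool over the recruitment period.** 200 × 1.5 years = 300 eligible.

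**Step 3: the target implied by 25%.** 300 × 0.25 = 75, or 75/18 = 4.17 a month. The planned 60 is 60/18 = 3.33 a month, which is 15 patients (one fifth) fewer.

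**Step 4: the proportion implied by 60.** 60/300 = 20.0%. The planned figure is reproduced exactly by 20% and not by 25%.

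**Step 5: precision.** The exact (Clopper-Pearson) 95% CI for 60/300 is 15.6% to 24.98%, so 25% lies at the upper limit.

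**Step 6: what would link 60 to 25%.** 60/0.25 = 240 eligible, and 240/200 × 12 = 14.4 months. An allowance equal to 18 − 14.4 = 3.6 months of full-rate screening would close the gap. The article states no such allowance. The exact 95% CI for 60/240 is 19.7% to 31.0%.

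**Step 7: the two proportions side by side.** With 300 eligible, 60 to 74 randomised patients would meet the 20% minimum and fall short of 25%.

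**Step 8: what the 506 target asks of the added centres (illustration).** Suppose the six centres keep supplying 200 a year, that is 600 in 3 years, and feasibility patients are not counted.
- At 25%: 506/0.25 = 2024 eligible are needed, so 1424 must come from nine centres. That is about 53 per centre per year.
- At 20%: 506/0.20 = 2530 are needed, so 1930 must come from nine centres. That is about 71 per centre per year.
- The first six average 200/6 = 33 per centre per year. If the nine were the same size, 15 centres would supply 33.3 × 15 × 3 = 1500 eligible, giving 375 randomised at 25% and 300 at 20%.

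The article does not give the size of the added centres, so this step shows only that the step from 25% to 20% matters and has not been calculated.

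**The case against.** The strongest defence concerns the progression criteria. A minimum may legitimately sit below the planning value, and the criteria are called guidelines. A reader might infer that the sponsor could go ahead on 20% alone. The text does not support that: 20% is worded as a necessary minimum, and the power guideline stands beside it. A 20% rate that could not deliver 506 would fail that other guideline. For the same reason it goes too far to say that one section flatly contradicts the other. What remains is that nothing shows 20% to be compatible with the power guideline, or reconciles it with the Sample size section's statement that about 25% is what gives confidence.

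A reader might also infer that reaching 60 can never demonstrate 25%. That holds only if recruitment takes the full 18 months with 300 eligible. Sixty reached from 240 eligible would be 25%. The proportion will use recorded eligible numbers, and the Discussion admits that these are poorly known beforehand. The point is therefore limited to the plan's own expected figures.

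It is also tempting to object that a true rate of 20% would pass the 20% minimum about half the time (0.52 with 300 eligible). That is no defect. Any threshold behaves so when the true rate equals it: 60 or more of 240 at a true 25% has probability 0.525.

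Nor is 60 the only figure with a numerical justification, since the article also gives a calculation for 506. Finally, the word approximately does not absorb the gap. Sixty is one fifth below 75, and the progression section itself treats 20% and 25% as different values.

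**Conclusion.** The point stands in limited form and should be fixed. On the article's own figures, 25% over 18 months implies 75 patients, and 60 implies 20%. If the full period is used and the expected 300 are eligible, meeting the target shows 20% (exact 95% CI 15.6% to 25.0%). An observed rate from 20% up to 25% would meet the progression minimum but fall short of the rate named in the Sample size section, and no calculation shows that 20% would still support the definitive trial.

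The arithmetic rests on 200 eligible a year throughout and on no unstated start-up allowance. It does not depend on the size of the nine added centres. No effectiveness claim is affected, because the study is descriptive. What is affected is the basis for deciding whether to proceed.

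**What to change.** 1. In the Sample size section, do one of three things:
   - state that 60 in 18 months corresponds to 20% of the expected 300 eligible;
   - keep 25% and restate the target as 60 randomised out of about 240 eligible, about 14.4 months at 200 a year;
   - state the start-up allowance that links 25% to 60.
2. Use one required proportion in the Sample size section and the criteria for progression. Alternatively, keep the 20% minimum and show by calculation, with the assumed size of the nine added centres, that it still delivers 506 participants in 3 years with 15 centres.
3. Judge the proportion on all recorded eligible patients over the recruitment period, and report its 95% CI beside the threshold. The Statistical analyses section already plans CI estimation in general terms.

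Cost: changes to two sections and perhaps one short calculation, with no extra patients. The progression criterion may become stricter, or the stated rate less favourable. If the minimum itself is raised, that is a change of substance to be agreed before the results are seen.
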